Episiotomy is an incision in the area between the perineum and the anus, performed to enlarge the perineum and facilitate the process of natural childbirth, especially in primiparous women (1-3). This intervention is associated with side effects such as pain (3-5). Studies have shown that approximately 30% of women experience pain in the first two weeks, and 7% experience it up to 3 months after natural delivery (6). Due to the lack of direct observation of the mother and the proximity of the wound area to the anus, there is a possibility of wound infection (7-9). Discomfort after episiotomy affects the quality of life of both the mother and the baby (3, 10, 11). Considering that the baby requires the mother's presence and support for growth and development, especially in the early days after birth, it is crucial to pay attention and provide support to mothers who have undergone an episiotomy (7, 12). Since Iran's current policy is to increase the birth rate and population, more attention should be paid to prenatal and post-pregnancy care, especially for vaginal childbirth. An unpleasant experience during childbirth can affect a mother's future pregnancies and may lead to her deciding not to have more children, ultimately reducing population growth (6). On the other hand, if episiotomy is not used, there is a risk of perineal tears that may cause problems for the mother, such as a reduced quality of sexual life (4, 13) and difficulties with breastfeeding (2, 14). To alleviate the pain intensity of episiotomy and facilitate its faster healing, various treatment methods, including oral, rectal, and sitz baths, are used (12, 15). Due to the high costs and complications of treatment with chemical drugs (4), it is better to use herbal drugs, as recommended by the World Health Organization (16). It appears that plant oils, such as olive oil and black seed oil, may be effective in promoting the healing and repair of perineal wounds (16, 17). According to studies, many medicinal plants, especially olive oil, can accelerate wound healing and reduce pain and complications caused by episiotomy (14, 18). Olive oil is rich in substances that provide it with antimicrobial, antifungal, and anti-inflammatory properties (19, 20). These include phenolic compounds that promote cell repair, antioxidants that help reduce inflammation, and oleocanthal that can alleviate pain (12, 18, 21). Olive oil has been found effective in treating skin diseases, suppressing the growth of viruses and bacteria, and promoting wound healing (12, 22).

Black seed contains 30% to 40% oil and is particularly rich in a type of antioxidant called thymoquinone (23, 24), as well as phenols, linoleic acid, and oleic acid, which have been the subject of various studies demonstrating their positive effects on wound healing (25). Studies have shown that black seed is suitable for promoting wound healing in the human body and can help prevent infections (26, 27). Furthermore, adding black seed oil to olive oil enhances its antioxidant properties (28). Given the limited number of human clinical studies on black seed oil and the scarcity of research regarding the local effectiveness of the combination of olive oil and black seed

oil in alleviating pain and promoting episiotomy wound healing, the present study aims to evaluate the effectiveness of the combination of olive and black seed oil in reducing pain intensity and facilitating episiotomy wound healing in primiparous women.

## **Review of texts**

1. Reda M. Hables (2021) conducted a study with the aim of comparing and investigating the effect of olive oil, lavender and placebo on 120 women at Al-Shatabi Hospital in Egypt. The samples were randomized into three groups receiving lavender, olive oil or vegetable oil as a placebo. The first group was treated with 10 drops of two percent lavender oil in five liters of water, the second group was treated with olive oil sitting bath (10 drops in five liters of water) and the third group was treated with a placebo with the same method as the second group for 14 days. Pain intensity was assessed by Visual Analog Pain Scale (VAS) and redness, edema and discharge were assessed by REEDA scale. On the first day, the pain score and REEDA score were not significantly different between the three groups, but there was a significant difference between the three groups on the fifth, ninth and fourteenth days after episiotomy. The result of the study showed that the use of olive or lavender oil is effective in reducing the damage to the perineum caused by episiotomy and its repair (6). This study was in the form of a sitting bath in warm water, but the present study will be in the form of topical application of olive oil and black seed.
2. Nahid Barati and Masoumeh Kordi (2020) conducted a clinical trial study titled the effect of black seed cream on episiotomy pain. This study was conducted on 124 primiparous women of Vali Asr Hospital in Birjand. The samples were randomly divided into three groups: black seed cream, placebo (cold cream) or routine care. Four hours after episiotomy, both placebo and black seed cream groups used the creams in the amount of 20 grams twice a day for 10 days. And the control group received usual care. Pain intensity was assessed before the intervention, 12 hours after the intervention, and on the seventh and tenth days after the intervention by the McGill questionnaire. There was no significant difference in the pain intensity in the three groups before the intervention and 12 hours after, but on the seventh and tenth days after the intervention, the pain intensity in the group receiving black seed cream was far less than the other two groups. The results of this study showed that black seed cream reduces the intensity of pain caused by episiotomy. Therefore, it can be used as a non-pharmacological method (16). This study examined the effectiveness of black seed cream only on pain intensity. However, the present study will investigate the effectiveness of the combination of black seed oil with olive oil on pain intensity and episiotomy wound healing.
3. M. Kaviani et al. (2017) conducted a study with the aim of determining the effect of olive leaf extract ointment on reducing the intensity of episiotomy pain and its recovery. This

---

 Redness, Edema, Ecchymosis, Drainage, Approximation

randomized trial was conducted on 90 women including three groups of 30 people who used olive leaf ointment, placebo and betadine solution three times a day for 10 days locally in the episiotomy area. Data were collected 4 hours after delivery and on the third, seventh, tenth and fourteenth days after delivery. Wound healing was evaluated by REEDA scale and pain intensity was evaluated by Visual Analog Pain Scale. The findings of the study showed that there was a significant difference between the olive leaf extract ointment group and other groups in terms of wound healing and pain. And this ointment is effective in reducing pain intensity and early complications of episiotomy (14).

4. A study by Amani R. et al. (2015) was conducted on 90 primiparous women in hospitals affiliated to Gilan University of Medical Sciences, Iran. The aim of this study was to compare the effect of cold gel pad and topical olive oil on episiotomy wound healing. The samples were randomly placed in two groups receiving cold gel pads for 20 minutes at 12 hours after delivery and if needed for 10 days or topical olive oil twice a day at 12 hours and 10 days after delivery. Episiotomy wound healing was evaluated at 12 hours after delivery and on the fifth and tenth days with the REEDA scale. 10 days after delivery, there was a significant difference between the two groups in terms of redness, and based on this study, olive oil can accelerate episiotomy wound healing (17).
5. Bahmanesh et al. (2013) conducted a clinical trial with the aim of investigating the effect of olive oil sitz bath on improving perineal injury after childbirth. This study was conducted on 60 women who had mediolateral episiotomy or first- or second-degree tears. The samples were randomly divided into two treatment groups with olive oil sitz bath or distilled water sitz bath control group. The intervention group used olive oil sitting bath for 10 minutes twice a day for 10 days, 24 hours after delivery. In this way, five drops of olive oil were poured into five liters of water. The control group also used a sitting bath of distilled water in the same way. The data were evaluated in the first two hours after delivery, on the fifth and tenth days, using the visual pain scale and REEDA. The findings of the study showed that there was no significant difference in pain intensity and wound healing between the studied groups in the first two hours. However, on the fifth and tenth days, there was a significant difference in terms of pain intensity and wound healing between the two groups of olive oil and distilled water. As a result, it was suggested to use olive oil sitting bath in warm water for episiotomy care (12).

## **Objective and assumptions**

### **General goal**

Determining the effectiveness of olive and black seed oil combination in pain intensity and episiotomy wound healing in prim parous women referred to hospitals under the auspices of Babol University of Medical Sciences

### **Specific objectives**

- Comparison of the change in the average intensity of episiotomy pain in three groups receiving the combination of olive oil and black seed, olive oil alone and the routine care group in the first 10 days after delivery
- Comparison of the average change of episiotomy wound healing in three groups receiving the combination of olive oil and black seed and the routine care group in the first 10 days after delivery
- Comparison of side effects caused by drug use (burning and itching, episiotomy wound opening and need for re-repair) in three groups

### **Practical objectives**

If the combination of olive oil and black seed oil or olive oil alone is effective with a local method to reduce pain intensity and heal the episiotomy wound after natural childbirth, these substances can be used so that mothers can have a pleasant experience of childbirth with faster healing of the episiotomy wound have a natural the pleasant experience of natural childbirth will lead to the promotion of this importance and increase the motivation for having children again, which is part of the country's demographic policies.

### **Assumptions**

- The average change of episiotomy pain intensity is different in the three groups receiving the combination of olive oil and black seed, olive oil alone, and the routine care group for the first 10 days after delivery.
- Comparison of the average change of episiotomy wound healing in the three groups receiving the combination of olive oil and black seed and the routine care group is different in the first 10 days after delivery.
- Comparison of side effects caused by drug use (burning and itching, episiotomy wound opening and the need for re-repair) are different in the three groups.

### **Table of variables**

| Variable name        | Measurement method                                      | variable role | variable scale | Variable type    | Functional definition                                                                                                                                                                                                   |
|-----------------------------|----------------------------------------------------------------|----------------------|-----------------------|-------------------------|--------------------------------------------------------------------------------------------------------------------------------------------------------------------------------------------------------------------------------|
| Drug intervention           | questionnaire                                                  | Independent          | nominal               | Qualitative             | done/not done                                                                                                                                                                                                                  |
| Severity of episiotomy pain | 10cm pain ruler                                                | Dependent            | relative              | Quantitative/Continuous | Based on the person's statements, zero means the least pain and 10 means the most possible pain                                                                                                                                |
| Episiotomy wound healing    | REEDA scale                                                    | Dependent            | relative              | Quantitative/Continuous | Based on measuring the variables of swelling, bruising, redness and the distance between the two edges of the episiotomy wound in the lithotomy position. The score of each part is 0 to 3 and the total score is from 0 to 15 |
| Mrs. age                    | year                                                           | contextual variable  | relative              | Quantitative/Continuous | Counting the years of life based on the date of birth according to the person's statement                                                                                                                                      |
| [name]              | Illiterate, elementary, middle school, high school, university | contextual variable  | Rank variable         | Qualitative             | Based on the last educational qualification and according to the person's statements                                                                                                                                           |
| Address                     | City, village                                                  | contextual variable  | nominal               | Qualitative             | Based on individual statements                                                                                                                                                                                                 |
| husband's age               | year                                                           | contextual variable  | Rank variable         | Quantitative/Continuous | Counting the years of life based on the date of birth according to the person's statement                                                                                                                                      |
| Woman's job                 | Working at home, working outside the home, unemployed          | contextual variable  | nominal               | Qualitative             | Based on individual statements                                                                                                                                                                                                 |

|                                                  |                                                                                                                        |                      |               |                         |                                |
|--------------------------------------------------|------------------------------------------------------------------------------------------------------------------------|----------------------|---------------|-------------------------|--------------------------------|
| Husband's job                                    | Unemployed, farmer, employee, freelancer, specialist (engineering, medicine, judgment, etc.), manager, student, others | contextual variable  | nominal       | Qualitative             | Based on individual statements |
| The economic situation                           | Easy, not easy, not hard, sometimes hard, hard, I don't know                                                           | contextual variable  | Rank variable | Qualitative             | Based on individual statements |
| height                                           |                                                                                                                        | contextual variable  | relative      | Quantitative/Continuous | Based on individual statements |
| Weight                                           |                                                                                                                        | contextual variable  | relative      | Quantitative/Continuous | Based on individual statements |
| Having a fever during labor                      | no, yes                                                                                                                | intervening variable | nominal       | Qualitative             | Based on individual statements |
| Receive antibiotics in labor                     | no, yes                                                                                                                | intervening variable | nominal       | Qualitative             | Based on individual statements |
| Hospitalization of the baby in Special care unit | no, yes                                                                                                                | contextual variable  | nominal       | Qualitative             | Based on individual statements |
| Receiving antibiotics in the postpartum period   | no, yes                                                                                                                | intervening variable | nominal       | Qualitative             | Based on individual statements |
| painkiller                                       | Number of painkillers used                                                                                             | intervening variable | nominal       | Qualitative             | Based on individual statements |

## method

### Study population and sampling method

This randomized clinical trial will be conducted as a parallel-group, non-inferiority study on postpartum women who have undergone episiotomy in the hospitals of Babol city. The samples

will be included in the study by easy sampling method and then they will be randomly assigned into three groups.

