### Sample size

The sample volume was calculated at the confidence level of 95%, the power of the test was 80%, and according to the information of the article by Kurdi et al. (16) with values of  $\sigma_1=1.5$ ,  $\mu_1=5$ ,  $\sigma_2=2.2$ , and  $\mu_2=6.4$ , with the following formula and assuming dropout During the implementation, the number of 36 samples in each group is estimated.

$$n = \frac{(Z_{1-\alpha/2} + Z_{1-\beta})^2 (S_1^2 + S_2^2)}{(\mu_1 - \mu_2)^2}$$

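### The protocol labels the trial non-inferiority, but its hypotheses, sample size and tests are all for a difference, and no margin is given

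*Protocol*

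**What the plan says.** The design statement, in the protocol's section Study population and sampling method, reads: "This randomized clinical trial will be conducted as a parallel-group, non-inferiority study on postpartum women who have undergone episiotomy". This is the protocol's only mention of non-inferiority.

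The other parts that fix the question and the decision are these:

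- **Assumptions (the hypotheses).** For pain: "The average change of episiotomy pain intensity is different in the three groups". For wound healing, the comparison with "the routine care group is different in the first 10 days after delivery".
- **Practical objectives.** The intended use of the result begins: "If the combination of olive oil and black seed oil or olive oil alone is effective".
- **Sample size.** 95% confidence, 80% power, means of 5 and 6.4, standard deviations of 1.5 and 2.2, and a formula with the squared difference in means as its denominator. The result is 36 per group after an allowance for dropout whose rate is not stated.
- **Statistical analysis.** ANOVA, repeated measures, mixed models, and ANCOVA on the pre-intervention value, by intention to treat, with significance at P < 0.05. Mean differences with 95% confidence intervals are given to show effect size.
- **Data Collection and Management.** Three arms of 36: the oil combination, olive oil alone, and routine care only.

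**The concern.** A non-inferiority trial asks whether a treatment is worse than a named reference by less than a stated margin, and answers by comparing a confidence limit with that margin. A test of difference asks whether the null hypothesis of no difference can be rejected. A non-significant result means opposite things under the two: under the second it settles nothing, while under the first a reader may take it as success.

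The comparison most exposed is the combination against olive oil alone. Both arms receive an oil, so a small difference is plausible. If P exceeds 0.05 there, the label in the design statement invites the conclusion that one is not inferior to the other, although the protocol has no rule to support this.

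The label also fails to serve the stated aim. Showing that the oils are no worse than routine care would not show that they are effective, which is what the practical objectives need.

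**Working it through.** **1. Side-by-side reading.** Each element that a non-inferiority design needs, against what the protocol has:

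| Element | In the protocol |
|---|---|
| Hypothesis of being no worse than a reference by a margin | Hypotheses that the groups differ |
| Margin | None |
| Named reference arm for each non-inferiority comparison | None |
| Sample size with the margin in the denominator | Expected difference in the denominator |
| Confidence limit compared with the margin | P < 0.05; intervals only display effect size |

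The objectives, hypotheses, sample size and tests agree with one another. Only the design label disagrees.

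**2. The plan's own sample size.** Inputs from the Sample size section: SDs 1.5 and 2.2, means 5 and 6.4, two-sided alpha 0.05, power 80%.

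- Sum of variances: 1.5² + 2.2² = 2.25 + 4.84 = 7.09
- Difference: 6.4 − 5 = 1.4; squared, 1.96
- n = (1.960 + 0.842)² × 7.09 / 1.96 = 28.39, so 29 per group before dropout
- With 20% dropout (an assumption): 28.39 / 0.80 = 35.5, so 36. Rounding up to 29 first gives 29 / 0.80 = 36.25, so 37.

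The stated 36 is thus reproduced, under an assumed dropout near 20%, as the size for a two-sided test of difference. Power for a difference of 1.4 is 81% with 29 evaluable per arm and 88% with 36.

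**3. What a null result would leave open.** Unadjusted standard error of a pairwise difference: √(7.09/n).

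- n = 36: √(7.09/36) = 0.444; 95% half-width 1.96 × 0.444 = 0.87 cm
- n = 29: √(7.09/29) = 0.494; 95% half-width 1.96 × 0.494 = 0.97 cm

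**4. The margin at which the trial would have 80% non-inferiority power.** With a true difference of 0 and one-sided alpha 0.025, margin = (1.960 + 0.842) × standard error.

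- n = 36: 2.802 × 0.444 = 1.24 cm, or 1.24/1.4 = 89% of the assumed effect
- n = 29: 2.802 × 0.494 = 1.39 cm, or 1.39/1.4 = 99% of it

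**5. Smaller margins, as assumptions only.** Power = Φ(margin / standard error − 1.96); n per group for 80% power = (1.960 + 0.842)² × 7.09 / margin².

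| Assumed margin | Power at 29 | Power at 36 | n per group for 80%, before dropout |
|---|---|---|---|
| 0.7 cm | 29% | 35% | 114 |
| 1.0 cm | 52% | 62% | 56 |
| 1.4 cm | 81% | 88% | 29 |

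**6. Effect of baseline adjustment.** If the correlation between baseline and day-10 pain were 0.5 (an assumption), ANCOVA would multiply the standard error by √(1 − 0.25) = 0.866. The half-widths become 0.87 × 0.866 = 0.75 cm at 36 and 0.97 × 0.866 = 0.84 cm at 29. The 80% margins become 1.24 × 0.866 = 1.07 cm and 1.39 × 0.866 = 1.20 cm.

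**The case against.** The strongest reply is that this is one mistaken word. No objective, test or decision rule uses it. Analysed as written, the trial gives valid two-sided tests of difference at a size that reproduces, and the analysis section already promises mean differences with 95% confidence intervals. All of that stands, and it is why the repair is small. It does not make the design statement right: that statement names the framework in which readers will interpret the result.

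A second reply is that a separate SAP, not shown, may give a margin. It could not reconcile the protocol, whose own hypotheses and sample size use none.

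The numbers also need care. The margins of 0.7 and 1.0 cm are assumptions; the protocol proposes none. The unadjusted standard error ignores the planned ANCOVA, which may narrow the intervals. The SDs come from a cited trial of black seed cream and may not fit the combination against olive oil. The figures are therefore illustrations, not properties of the plan.

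Three stronger readings are tempting and are not supported:

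- A reader might infer that the investigators intend to report a null result as non-inferiority. No section says so; the label only leaves the door open.
- A reader might infer that 80% non-inferiority power is reached only if the margin equals the full 1.4. That is about right at 29 per arm (1.39) but not at the stated 36 (1.24).
- A reader might infer that the trial registration carries the same error. The protocol says only that the trial will be registered; the content of the record is unknown.

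**Conclusion.** The design label contradicts the hypotheses, the sample-size calculation and the decision rule, and nothing in the protocol reconciles them. The label is what is wrong; the sample size and tests agree with the stated hypotheses. Strictly, the hypotheses are non-directional, so the planned tests are two-sided tests of difference, for which superiority is the usual shorthand.

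On size: with the plan's SDs and no baseline adjustment, a non-significant pairwise pain comparison has an interval reaching about 0.87 cm either side of the estimate at 36 per arm (0.97 at 29). A non-inferiority claim with 80% power would need a margin of about 1.24 cm (1.39 at 29), close to the whole 1.4 the plan assumes as the effect. This rests on a true difference of 0 and on the cited SDs applying to each pair of arms. The contradiction itself rests on no assumption. It should not be read as a finding that 36 per group is too few for the test of difference on which it was calculated.

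**What to change.** In Study population and sampling method, replace the word non-inferiority with superiority, defined as a two-sided test of difference at alpha 0.05. In Statistical analysis, add one sentence: *A non-significant difference between groups will be reported with its 95% confidence interval and will not be interpreted as non-inferiority or equivalence.*

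The 36 per group and the tests stand. The cost is a protocol amendment of one word and one sentence, and giving up a non-inferiority claim that the design does not support.

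If the sponsor does intend non-inferiority, the protocol would instead need a justified margin, a reference arm for each comparison, a confidence-limit rule and a new sample size.
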